## Abstract

**Background:**

The first 1000 days after conception are a critical period to encourage lifestyle changes to reduce the risk of childhood obesity and early programming of chronic diseases. A healthy lifestyle during pregnancy is also crucial to avoid high post-partum weight retention. Currently, lifestyle changes are not consistently discussed during routine health services in Germany. The objective of this study is to evaluate a novel computer-assisted lifestyle intervention embedded in prenatal visits and infant check-ups. The intervention seeks to reduce lifestyle-related risk factors for overweight and obesity among expecting mothers and their infants.

**Methods:**

The study is designed as a hybrid effectiveness-implementation trial to simultaneously collect data on the effectiveness and implementation of the lifestyle intervention. The trial will take place in eight regions of the German state Baden-Wuerttemberg. Region were matched using propensity score matching. Expecting mothers (*n* = 1860) will be recruited before 12 weeks of gestation through gynecological practices and followed for 18 months. During 11 routine prenatal visits and infant check-ups gynecologists, midwives and pediatricians provide lifestyle counseling using Motivational Interviewing techniques. The primary outcome measure is the proportion of expecting mothers with gestational weight gain within the recommended range. To understand the process of implementation (focus group) interviews will be conducted with providers and participants of the lifestyle intervention. Additionally, an analysis of administrative data and documents will be carried out. An economic analysis will provide insights into cost and consequences compared to routine health services.

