### Data sources

Data will be collected at various points in time using multiple methods. Data sources include an electronic survey completed by study participants in the GeMuKi-Assist App at four points in time, data entered into the GeMuKi-Assist counseling tool during routine prenatal visits and infant check-ups, (focus group) interviews with multi-professional providers and intervention participants, statutory health insurance claims data and documents. At baseline, study participants also complete a short paper survey including demographic questions.

The selection of data sources was guided by the RE-AIM framework, which has been developed for evaluation of effectiveness and implementation of interventions in real-world settings [44, 45]. Table 1 provides a summary of constructs that will be measured for each dimension of the RE-AIM framework and data sources used.

**Table 1 Tab1:** Data sources and measured constructs aligned with RE-AIM dimensions

Dimension	Definition	Measured construct	Data source
Reach	The absolute number, proportion, and representativeness of individuals who are willing to participate in an initiative, intervention, or program.	Number and characteristics of participants and non-participants, reasons for non-participation	Administrative data in GeMuKi-Assist, focus groups with multi-professional providers, paper survey
Effectiveness	The impact of an intervention on important outcomes, including potential negative effects, quality of life, and economic outcomes.	Proportion of participants with excessive weight gain, infant body composition and weight development	Administrative data in GeMuKi-Assist
		Maternal lifestyle, knowledge, infant feeding, infant diet and physical activity	Electronic survey
Adoption	The absolute number, proportion, and representativeness of settings and intervention agents (people who deliver the program) who are willing to initiate a program.	Proportion and characteristics of participating multi-professional practices, reasons for non-participation and drop-out of practices	Administrative data in GeMuKi-Assist, documents and publicly available statistics
Implementation	*Setting level:* the intervention agents’ fidelity to the various elements of an intervention’s protocol, including consistency of delivery as intended and the time and cost of the intervention.	Implementation of brief lifestyle advice intervention (how and by whom?)	Focus groups with multi-professional providers,

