#### Maternal weight

During every prenatal visit maternal weight is routinely measured and documented in the maternity record booklet (see Table 2). GWG is calculated as the difference between self-reported pre-pregnancy weight documented during the first prenatal visit and weight at the last prenatal visit.

Excessive GWG is defined according to recommendations of the Health and Medicine Division of the National Academies of Science, Engineering and Medicine (previously known as Institute of Medicine, IOM). These recommendations differ depending on pre-pregnancy Body Mass Index (BMI). For underweight women (BMI < 18.5) the recommended weight gain ranges from 12.5 to 18 kg, for normal weight women (BMI = 18.5–24.9) from 11.5 and 16 kg, for overweight women (BMI = 25–29.9) from 7 to 11.5 kg and for obese women (BMI ≥ 30) from 5 to 9 kg [46]. Weight gain above the recommended range is classified as excessive GWG. This definition of excessive GWG is similar to the definition used in German guidelines, which currently recommend a maximum weight gain of 16 kg for normal weight women and a maximum of 10 kg for overweight and obese women [36]. To assess postnatal weight-retention, maternal weight data will also be collected 1 year after birth.

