### Sample size calculation

GWG was used as primary outcome for the sample size calculation, because healthy GWG is discussed with all expectant mothers participating in the lifestyle intervention. The brief lifestyle intervention is assumed to reduce the proportion of study participants with excessive gestational weight gain by 10%. Similar interventions have achieved a reduction in the proportion of excessive weight gain of around 20% [18, 59]. The target was set lower in this study, because the lifestyle intervention is implemented in a routine health service setting with less stringent inclusion criteria. To detect a 10% reduction in excessive gestational weight gain with a power of 80%, an alpha of 0.05 and an ICC of 0.05 a sample of *n* = 1240 pregnant women is required. This number was increased to *n* = 1860 to account for a drop-out rate of 25% in the intervention group and a 40% drop-out rate in the control group (see Fig. 1).

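### The abstract's primary outcome (weight gain within the recommended range) is not the outcome the sample size is powered for (excessive weight gain), and the two are not complements

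*Protocol article*

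**What the plan says.** The Methods paragraph of the abstract contains the article's only explicit designation of a primary outcome measure: "The primary outcome measure is the proportion of expecting mothers with gestational weight gain within the recommended range".

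The body uses a different category:

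- **Sample size calculation.** "GWG was used as primary outcome for the sample size calculation", a sentence that names no category of gain. The planning effect follows: "The brief lifestyle intervention is assumed to reduce the proportion of study participants with excessive gestational weight gain by 10" per cent. For this effect, "with a power of 80%, an alpha of 0.05 and an ICC of 0.05", the section concludes that "1240 pregnant women is required". That number is raised to 1860 for drop-out of 25% (intervention) and 40% (control).
- **Data sources, Table 1, Effectiveness row.** "Proportion of participants with excessive weight gain, infant body composition and weight development".
- **Maternal weight.** "Weight gain above the recommended range is classified as excessive GWG". The ranges are 12.5 to 18 kg (underweight), 11.5 to 16 kg (normal weight), 7 to 11.5 kg (overweight) and 5 to 9 kg (obese), each with a lower and an upper limit.

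The article gives no control-arm rate for any category of gain and no cluster size. It does not say whether the 10% is absolute or relative.

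**The concern.** With a lower and an upper limit there are three groups: below, within and above range. The abstract's outcome separates the within-range women from the other two groups. The powered outcome separates the above-range women from the other two. A woman below range is unfavourable on the first and favourable on the second.

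An intervention that lowers weight gain can move women from above range to within range, and others from within range to below it. The first movement helps both outcomes. The second leaves the excessive outcome unchanged and worsens the within-range outcome. A trial that achieved exactly the planned fall in excessive gain could therefore show a smaller rise, or none, in the within-range proportion.

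What is at stake is which binary variable carries the confirmatory test, and whether the stated power belongs to it. The Discussion says the results are meant to inform a federal decision on roll-out and public funding, so readers need to know which result is the primary one.

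**Working it through.** **1. The plan's own figures.** The drop-out step reproduces exactly if the 1240 are split equally (the ratio is not stated): 620/0.75 + 620/0.60 = 826.7 + 1033.3 = 1860.

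The 1240 cannot be derived uniquely without a control rate and a cluster size. It does fit an absolute fall of 10 points in excessive GWG (two-sided alpha 0.05, power 80%, pooled two-proportion formula, design effect 1 + (m − 1) × 0.05):

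| Excessive, control vs intervention | n per arm before clustering | m | Total |
|---|---|---|---|
| 40% vs 30% | 356 | 16 | 1246 |
| 45% vs 35% | 376 | 14 | 1241 |
| 50% vs 40% | 388 | 13 | 1242 |

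A relative 10% reduction does not fit. For control rates from 60% down to 30% it needs 2136 to 7108 women before any design effect. The absolute reading is thus an inference from the arithmetic and is not stated in the article.

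**2. How the two outcomes are linked.** Let excessive GWG fall by 10 points and let the below-range group grow by s points. The three proportions sum to 100%, so the within-range proportion rises by 10 − s points. The effects are equal only when s = 0.

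**3. Illustration of size.** Assumed, not from the article: control rates of 45% excessive, 35% within and 20% below; 620 evaluable women per arm. The design effect is back-solved as 620/376 = 1.65, equivalent to m = 14 at the stated ICC of 0.05. It is chosen so that power on excessive GWG is 80%, so that 80% is an input and not a finding.

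With w1 = 0.35 and w2 = 0.45 − s (s as a proportion):

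SE = √{[w1(1 − w1) + w2(1 − w2)] / 620 × 1.65}, power = Φ((w2 − w1)/SE − 1.96)

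| s (points) | w2 | SE | (w2 − w1)/SE | Power |
|---|---|---|---|---|
| 0 | 0.45 | 0.0356 | 2.81 | 80% |
| 2 | 0.43 | 0.0355 | 2.26 | 62% |
| 3 | 0.42 | 0.0354 | 1.98 | 51% |
| 5 | 0.40 | 0.0353 | 1.42 | 29% |

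The pooled formula agrees to within about one point. If all 10 points went below range, the within-range proportion would not change and the rejection rate would be alpha.

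**4. Other assumed control rates.** Excessive was varied over 40–50% and below range over 15–25%, with the design effect re-solved each time. Power on the within-range outcome is 76% to 86% with no shift and 27% to 34% with a 5-point shift.

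**5. Evaluable women for 80% power on the within-range outcome, base case.** About 1923, 2500 and 4851 for shifts of 2, 3 and 5 points, against 1240 planned.

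**The case against.** The strongest reply is that the abstract merely restates one endpoint in positive terms. The Maternal weight section calls the trial's definition similar to that in German guidelines, which give only a maximum gain. Under a maximum-only rule, being within the recommendation is the complement of being excessive. The body uses excessive gain consistently, so a drafting slip in one abstract sentence is a plausible explanation. This does not remove the conflict, because the ranges the trial adopts have lower limits, and read literally the abstract's sentence names another variable.

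Other parts of the reply stand:

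- Table 1 and the Maternal weight section do not rank outcomes. That excessive GWG is primary is an inference from the sample size section.
- A reader might infer that the team is free to pick an endpoint once the data are seen. The article does not show this. The trial was registered on 3 January 2019, in the month recruitment of participants began, and an analysis plan may exist. Either could already fix the outcome.
- A reader might take 62%, 51% or 29% as the trial's real power. They rest on an assumed control split, an assumed shift and a back-solved design effect. The article gives no basis for any particular shift. Providers in the intervention regions see each woman's gain plotted against the recommended range, so the shift could be small.
- A reader might conclude that the abstract must be the text in error. The article alone cannot settle that.

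**Conclusion.** The inconsistency is real and needs no outside source: the one explicit statement of the primary outcome names within-range GWG, and the 80% power and 1240 evaluable women belong to excessive GWG. The two are different variables by the article's own ranges, so the power statement does not automatically apply to the abstract's outcome.

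Different verdicts on the two outcomes are possible, not certain. They depend on how many women shift below range. With no shift the absolute effects are equal and power is similar. With a shift of a few points the illustration shows a substantial loss. It conveys direction and scale only, and the case for correction rests on the text. Because the point concerns the identity of the primary endpoint, it should be settled before analysis.

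**What to change.** Before analysis, name one primary GWG outcome in identical terms in the abstract, the Maternal weight section, Table 1 and the sample size paragraph, in line with what was pre-specified.

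- **If that is excessive GWG:** correct the abstract.
- **If that is within-range GWG:** restate the power and its assumptions for that outcome at the planned sample size, including an assumed shift below range.

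In either case, state the control rate and cluster size used, and whether the 10% is absolute. Make the other outcome secondary and report below, within and above range by arm, so that a shift into low gain is visible.

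The first branch costs a wording change and one descriptive table. The second adds a short recalculation, which may show less than 80% power. Neither needs new data collection.

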**Discussion:**

Findings of this study will add to the evidence on lifestyle interventions to reduce risk for overweight and obesity commenced during pregnancy. Insights gained will contribute to the prevention of early programming of chronic disease. Study results regarding implementation fidelity, adoption, reach and cost-effectiveness of the lifestyle intervention will inform decisions about scale up and public funding.

**Trial registration:**

German Clinical Trials Register (DRKS00013173). Registered 3rd of January 2019, https://www.drks.de

## Introduction

Overweight and obesity are increasing worldwide [1]. More than one in two adults and nearly one in six children are overweight or obese in OECD countries [2]. In Germany 35.9% of the adult population are overweight and 18.1% are obese [3]. Among children and adolescents 15.4% are overweight and 5.9% are obese [4].

The high prevalence of overweight and obesity represents a key risk factor for non-communicable diseases, including cardiovascular diseases, diabetes, musculoskeletal disorders and some cancers [1]. As childhood overweight and obesity tend to persist into adulthood [5], early interventions are essential.

There is growing evidence that lifestyle factors in the first 1000 days after conception are important predictors of childhood overweight and obesity. Maternal gestational weight gain (GWG), smoking and diet have been identified as predictors during pregnancy [6–10]. Rapid infant weight gain, nicotine exposure and infant feeding practices have been identified as essential factors after birth [6, 10–13].

Human epidemiology and animal model studies suggest that exposure to these factors affects developmental processes, which program susceptibility to obesity and other chronic conditions manifesting later in life [14, 15]. Pregnancy and early infancy therefore represent a critical period for targeted prevention efforts.

Lifestyle changes initiated during pregnancy also produce benefits for expecting mothers. Evidence suggests that adequate GWG can avoid high post-partum weight retention and thus reduce the risk of overweight and obesity following pregnancy [16, 17].

Several preventive interventions addressing maternal lifestyle during pregnancy have been evaluated. Two meta-analyses show that diet and exercise interventions during pregnancy can effectively reduce excessive gestational weight gain [18, 19]. There is also evidence that professional-led educational interventions can increase uptake of breastfeeding [20]. A Cochrane review indicates that counseling interventions during pregnancy can effectively increase smoking cessation rates [21]. High post-pregnancy relapse rates call for strategies to promote continued abstinence post-partum, however [21, 22].

Lifestyle intervention trials initiated during pregnancy that continue during infancy are scarce [23–25]. They are heterogeneous, have methodological limitations and have produced mixed results [23, 24]. Few intervention studies provide evidence for beneficial effects on growth status of infants or children of obese women only [24].

Interventions targeting multiple lifestyle related risk factors hold promise for more effective childhood obesity prevention [10, 26]. So far, intervention studies targeting feeding, diet and physical activity behaviors in combination with prenatal nicotine exposure are lacking [23].

The GeMuKi project (acronym for “Gemeinsam Gesund: Vorsorge plus für Mutter und Kind” - Strengthening health promotion: enhanced check-up visits for mother and child) aims to incorporate a brief multifactorial lifestyle intervention into routine prenatal visits and infant check-ups. In Germany, these check-ups currently focus on early identification of diseases and developmental problems only. Existing guidelines for pre- and postnatal care mention that providers have a role in discussing modifiable lifestyle factors, but they do not specify content or format of lifestyle counseling [27].

Recent findings of the GeliS trial (acronym for "Gesund leben in der Schwangerschaft") conducted in the German state of Bavaria suggest that incorporating lifestyle counseling into routine prenatal health services is feasible and leads to high compliance rates [28]. The lifestyle intervention itself achieved only slight improvements in prenatal intake of food items, exclusive breastfeeding behavior and maternal post-partum weight development [29, 30]. By continuing lifestyle counseling after birth and utilizing theoretically underpinned Motivational Interviewing (MI) techniques, the GeMuKi intervention addresses some limitations of the GeliS intervention. In addition, the GeMuKi intervention includes a novel shared telehealth platform to support multi-professional providers in the counseling process with a corresponding App for intervention participants.

The objective of this study is to examine effectiveness of the GeMuKi intervention and explore its potential for widespread implementation. It will answer the following research questions:
Does the GeMuKi intervention effectively improve lifestyle-related risk factors for overweight and obesity in expecting mothers and their infants compared to routine practice?How does implementation of the GeMuKi intervention take place in practice? What factors facilitate or hinder successful implementation during routine prenatal visits and infant check-ups?What costs, health service use and consequences are associated with the GeMuKi intervention from a public payer perspective? How do these compare to routine health practice?

## Methods/design

### Study design

A hybrid effectiveness-implementation trial (Type II) is being used to simultaneously collect data on the effectiveness and implementation of the GeMuKi lifestyle intervention [31, 32]. This design was selected because there is strong evidence that interventions during pregnancy can effectively improve lifestyle-related risk factors, research indicates that lifestyle counseling during routine check-up visits is feasible in Germany and evidence on implementation of lifestyle interventions during pregnancy is scarce. The GeMuKi intervention comprises various components previously identified to enhance lifestyle counseling during pregnancy. To our knowledge, effectiveness of these components has not been evaluated in combination, yet.

The trial has two arms (see Fig. 1). In the intervention arm gynecologists, midwives and pediatricians carry out the GeMuKi lifestyle intervention during routine prenatal visits and infant check-ups. In the control arm they provide care as usual. The study takes place in both urban and rural areas within the German state Baden-Wuerttemberg. To reduce discrepancies between study regions intervention and control regions were matched into pairs using propensity score matching. Matching was conducted immediately after the project kick off in October 2017 to provide enough time for enrollment of multi-professional providers and for conducting implementation training in the intervention regions before commencing recruitment of study participants. Matching was based on average income per capita, the number of births among persons insured by BARMER (i.e. the statutory health insurer agreeing first to participate in the GeMuKi project) and the number of gynecologists in the study regions. This resulted in four matched study region pairs, which were randomized into intervention and control regions.

**Fig. 1 Fig1:**
[figure not shown]
Study design flow chart

Data regarding effectiveness and implementation will be collected at multiple time points over an 18-month study period (see Table 2).

### Recruitment procedure

Recruitment of multi-professional providers commenced in April 2018 and continues until December 2019. For this purpose, informational meetings are being conducted in the study regions. Regional opinion leaders are attending these meetings to raise awareness of the GeMuKi project and promote participation from a user-perspective. Additionally, the project is advertised through professional organizations, journals, conference presentations and through contacting providers directly over the phone and during personal visits.

Recruitment of study participants commenced in January 2019 and continues until September 2020. It takes place during routine prenatal visits conducted in participating gynecologist practices before 12 weeks of gestation. Gynecologists determine eligibility of pregnant women using pre-defined in- and exclusion criteria. They provide eligible women with a project brochure and additional information about the study. For each study participant, who enrolls in the study, gynecologists receive an expense allowance of 20€.

### In- and exclusion criteria

Pregnant women are eligible to participate, if they provide informed consent, are ≥18 years old, are < 12 weeks of gestation at recruitment, are proficient in German language and are enrolled in one of the participating gynecologist practices. To participate in the study, pregnant women also require a health insurance plan from BARMER or from one of the following statutory health insurers, who became project partners upon commencement of the GeMuKi project: AOK Baden-Württemberg, Techniker Krankenkasse and through GWQ Service Plus: Audi BKK, BAHN-BKK, Bertelsmann BKK, BIG direkt gesund, BKK Deutsche Bank AG, BKK Schwarzwald-Baar-Heuberg, BKK Voralb HELLER *Index* LEUZE, Daimler BKK, Die Schwenninger Krankenkasse, energie-BKK, Heimat Krankenkasse, Salus BKK, SBK Siemens-Betriebskrankenkasse, SECURVITA Krankenkasse.

Pregnant women who screen positive for depression (i.e. defined as a sum score of > 9 or a score = 3 on item 10 of the Edinburgh Postnatal Depression Scale) are excluded from the study. They are referred to information about the ‘Mind: Pregnancy’ trial, which takes place simultaneously in the same study regions [33]. It evaluates an intervention to reduce psychological stress during pregnancy. This procedure aims to reduce risk of bias that could be introduced by co-interventions.

